**Statistical Power**

Our previous trial of placebo effects in IBS produced effect sizes that ranged from d=.5 to d=.9. Using two-tailed t-tests with alpha set at .05, a total sample size of 80 will have 60% power to detect the lower end of this range and 94% power to detect the upper end of the range. Using the same assumptions but a total sample size of only 50, we would have power between 41% and 88%.

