#### F. DESCRIPTION OF RESEARCH PROTOCOL

#### Overview: This RCT seeks to determine whether non-deceptive (open-label) administration of placebo pill produces significantly more clinical improvement in IBS patients than an observation control.

#### Overall Design: Eighty patients with IBS will be randomized to a three-week course of either 1: non-deceptive open-label placebo pill in the context of positive expectation + usual care or 2. No treatment + usual care. Both groups will receive an equal amount of time with the practitioner. Patients will be assessed at baseline, mid-point and at the end of three weeks with the standard outcomes measures for IBS.

| Figure 1: Study Flow Chart  Open Label +usual care  (N=40)  No treatment waitlist+ usual care (N=40)  Baseline Evaluation and Randomization  (N=100)  Midpoint  Evaluation  Midpoint  Evaluation  3 Week Endpoint  Evaluation  3 Week Endpoint  Evaluation |
| --- |

Restatement of Research Question: A three-week course of non-deceptive open label placebo treatment will be produce statistically superior outcomes to a no treatment waitlist control group.

Design methodology and intervention:

Description of the non-deceptive placebo treatment arm: The intervention will

be geared to maximizing the contributions of positive expectation,

conditioning, adherence and a supportive and confident patient

practitioner relationship to the placebo response of IBS patients taking an

open-label placebo pill. The first phase of the discussion will be designed

to enhance expectation. Patients will be asked whether they have heard of

the placebo effect and what they think of it. After a brief exchange geared

to supporting any positive feelings the patient may have about placebo effects,

the practitioner will then talk about the evidence supporting the idea that just

taking placebo pills with a positive expectation initiates still poorly understood

effects that can have a profound impact of illness. It will be clearly explained that

placebo are made of "inert" substances like sugar pills but have been show

in clinical trials to improve patient symptoms. The practitioner will discuss

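### The 94% power quoted for d = 0.9 with 80 patients does not follow from the stated t-test: that test gives 98%, and 94% corresponds to d = 0.8

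*Protocol*

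**What the plan says.** The Statistical Power section of the protocol is its only sample-size justification. It reports that the previous placebo trial in IBS "produced effect sizes that ranged from d=.5 to d=.9". The method is given as "Using two-tailed t-tests with alpha set at .05". On that basis the power for 80 patients is put at 60% for d = 0.5. For d = 0.9 the claim is "94% power to detect the upper end of the range". It then keeps the assumptions the same and considers a smaller trial: with "a total sample size of only 50, we would have power between 41% and 88" per cent.

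Under Overall Design the protocol states that "Eighty patients with IBS will be randomized to a three-week course", and the flow chart there shows 40 patients in each arm. The power paragraph mentions no dropout allowance, unequal allocation or other significance level.

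**The concern.** The paragraph gives four power figures from two sample sizes and two effect sizes, with one test and one alpha. All four should come from the same calculation. The figure for 80 patients at the upper effect size looks too low beside the others.

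The paragraph exists to show what 80 patients achieve and what would be lost with 50. If one upper figure rests on a different effect size from the other, that comparison is not like for like. It also puts the upper end of the planning range in doubt. The protocol says this trial is to supply preliminary data for a larger grant application, so the effect range may be reused.

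**Working it through.** **Inputs.** From Statistical Power: d = 0.5 and 0.9, two-sample t-test, two-sided alpha .05, total N of 80 or 50. From the flow chart under Overall Design: 40 per arm at N = 80. Equal arms (25 each) are assumed at N = 50.

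**Formula.** With n per arm, the t statistic has 2n − 2 degrees of freedom and noncentrality δ = d·√(n/2). Power is the probability that a noncentral t variable with that δ falls outside the two-sided 5% critical values.

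- n = 40: √20 = 4.472, 78 degrees of freedom
- n = 25: √12.5 = 3.536, 48 degrees of freedom

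**The four printed figures.**

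| Total N | d | δ | Power computed | Power printed |
|---|---|---|---|---|
| 80 | 0.5 | 2.236 | 59.8% | 60% |
| 50 | 0.5 | 1.768 | 41.0% | 41% |
| 50 | 0.9 | 3.182 | 87.7% | 88% |
| 80 | 0.9 | 4.025 | **97.8%** | **94%** |

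Three of the four agree to the rounded per cent, which confirms the method and inputs. The fourth differs by 97.8 − 94 = 3.8 points. The choice of formula does not explain this: the normal approximation gives Φ(4.025 − 1.960) = Φ(2.065) = 98.0%.

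**Could another effect size account for it?** Solving for d at N = 80 and 94% power gives 0.796. Solving at N = 50 and 88% power gives 0.905. Trying single values for both sample sizes:

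| d | N = 80 | N = 50 |
|---|---|---|
| 0.80 | 94.2% | 79% |
| 0.85 | 96.4% | 83.8% |
| 0.90 | 97.8% | 87.7% |
| Printed | 94% | 88% |

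No row gives both printed values.

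**Could an unstated assumption account for it?** Each variant below is applied at N = 80 unless stated, and must also keep the printed 60% at d = 0.5.

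| Variant | d = 0.9 | d = 0.5 |
|---|---|---|
| Two-sided alpha .025 | 95.7% | 48.4% |
| Two-sided alpha .01 | 91.4% | 34.9% |
| One-sided alpha .05 | 99.1% | 71.6% |
| 2:1 allocation | 96.3% | 54.9% |
| 3:1 allocation | 93.1% | 48.1% |
| 20% dropout (32 per arm) | 94.3% | 50.4% |
| Total N = 100 | 99.4% | 69.7% |

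The last row is included because section C and the top box of the flow chart mention 100 patients. The variants that come near 94% depart from the stated inputs and pull the lower figure well below 60%. None gives both 94% and 60%.

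**Effect on the comparison of sample sizes.** As printed, the gain from 50 to 80 patients at the upper effect size is 94 − 88 = 6 points. At d = 0.9 throughout it is 98 − 88 = 10 points. At d = 0.8 throughout it is 94 − 79 = 15 points.

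**The case against.** The strongest reply is that nothing in the design depends on this number. On the stated d = 0.9 the error understates power, 80 patients are ample at that effect size with either figure, and the limiting figure of 60% at d = 0.5 is correct. The primary outcome is also a responder proportion on the IBS-GIS, compared by chi-square, so a t-test power figure bears directly only on the continuous outcomes. All of this stands, and it limits the consequence. It does not make the printed figure right.

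A second reply is that the range is stated plainly as ending at 0.9 and the 88% for 50 patients supports that, so d = 0.8 need not be considered. This has force. The document names 0.9 and never 0.8, and the error could be a slip in copying. That 94% came from a calculation at d = 0.8 is an inference from the close match, not something the protocol says. For that reason 98% is the natural correction, and the d = 0.8 alternative applies only if the sponsor's source shows that the range ended there. In that case the error would not be conservative: the top of the range and the power for 50 patients would both be overstated.

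**Conclusion.** The point holds. Under the protocol's own inputs (two-sample t-test, two-sided alpha .05, 40 per arm, d = 0.9, no dropout allowance) power is 97.8%, against 94% printed. The paragraph is internally inconsistent, because its two upper figures imply different effect sizes, about 0.80 for 80 patients and about 0.90 for 50. The comparison of 80 with 50 patients therefore understates the gain from the larger trial, on either reading of the upper effect size. The choice of 80 patients, the 60% at d = 0.5 and the planned analyses are unaffected. Which effect size was intended can be settled only from the sponsor's source for the previous trial's range.

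**What to change.** Check the upper effect size against the previous trial's results, then make one of two corrections in Statistical Power:

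- If the range ends at d = 0.9, as written, change 94% to 98% for 80 patients. The 88% for 50 patients stays.
- If the range ended at d = 0.8, change 0.9 to 0.8 and change the upper figure for 50 patients from 88% to 79%. The 94% stays.

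The first changes one number in one sentence and the second changes two numbers. Neither alters the sample size, the conduct of the trial or the analysis.

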**G. Subject Selection**

| **Subject Selection:**  Patients will be recruited from the BIDMC GI Clinic and through IRB approved advertisements.  **Inclusion/Exclusion Criteria:**  Inclusion Criteria:   1. Only adults (>18 years of age) meeting the Rome III Criteria for IBS will be eligible for entry into the study. 2. Patients with ‘warning symptoms’ (e.g., unexplained weight loss, family history of colon cancer or inflammatory bowel disease, and rectal bleeding) will be required to have had a detailed workup to exclude organic pathology prior to enrolling the patient. 3. Participants will be allowed to continue their IBS medications (e.g., fiber, anti-spasmodics, antidepressants, loperamide, etc.) as long as they had been on stable doses for at least 30 days prior to entering the study and agreed not to change medications or dosages during the trial. 4. Patients will be asked not to make significant changes to their diet during the study. 5. In addition, patients will be required to have active symptoms at the entry of the study as defined by having an IBSSSS score of >150 (0-500 scale).   Exclusion Criteria:   1. Patients will be excluded if they had abdominal surgeries (excluding cholecystectomy, appendectomy, hysterectomy, and hernia repair). 2. History of inflammatory bowel disease (e.g., ulcerative colitis, Crohn’s disease). 3. Recent antibiotic use (within 1 month). 4. Radiation proctitis or other known poorly controlled medical conditions that could interfere with bowel function. 5. Patients will be excluded if they on narcotics or other pain medications (except for non-steroidal anti-inflammatory drugs). 6. Patients will also be required to have active symptoms at the time of entry into the study (score of >150 on the IBS-SSS). 7. Previous experience participating in randomized controlled trials for IBS. |
| --- |

#### H. Possible Benefits

| The patient may or may not benefit from participating in this study. The open placebo may help their Irritable Bowel Syndrome symptoms i.e. their symptoms may be lessened by taking the placebo in the context of positive expectations. The patient’s participation in the study may also help researchers develop more effective medications for treating symptoms of Irritable Bowel Syndrome. |
| --- |

#### I. Possible Risks

| Safety Measurements  The safety of subjects will be monitored at each study visit  - AEs  -Vital signs and body weight  - Physical exam  - Concomitant medication use  *Risks:*  *Subjects may experience normal fluctuations in their IBS symptoms (i.e., abdominal pain or discomfort). But since no active treatment is being given and patients are being evaluated 3 times over 3 weeks by a practitioner experienced in IBS there is minimal risk to the patient.* |
| --- |

## J. Study Location

| Study visits will be conducted in the Division of Gastroenterology, BIDMC in Rabb Rose 1 or alternatively in the GI Motility Center, Stoneman 4 East Campus. |
| --- |

## K. Data Security

| Data will be kept in a locked room that only individuals listed above have access to. Any PHI used by the study sponsor will be assigned a number with the patient’s initials. Files may be kept for a minimum of 6 years, kept in a locked, secured file cabinet or computer in a locked room that only individuals listed above have access to. The sponsor will be contacted prior to destroying files upon archive expiration. |
| --- |
